## 1. Introduction

### 1.1. Background

Neonatal mortality (infant death within 28 days of birth) remains a significant health concern worldwide, accounting for nearly half of all deaths in children under five years of age, with the majority occurring in low-to-middle-income countries (LMICs) [1,2]. In Sierra Leone, the neonatal mortality rate (NMR) remains high at 31 per 1000 live births, far exceeding the Sustainable Development Goal 3.2 (SDG) target of 12 per 1000 [3,4]. Reducing neonatal mortality and morbidity is thus a high priority.

Neonatal respiratory distress is the leading cause of neonatal morbidity and mortality in the first week of life. Immediate recognition of respiratory distress, followed by prompt resuscitation and follow-on care, is critical for survival [5,6,7,8,9]. The results of previous studies have demonstrated that implementation of bundled newborn care interventions, including resuscitation training and respiratory support, can significantly reduce neonatal mortality. For example, the “Safer Births Bundle of Care” program in Tanzania, which implemented low-dose, high-frequency resuscitation training and skills mentoring for midwives, recently demonstrated a 40% reduction in neonatal deaths in the first week of life [10].

Continuous positive airway pressure (CPAP), delivered as either mechanical or bubble CPAP, plus oxygen blenders improve neonatal respiratory distress outcomes by preventing hyperoxic lung injury and retinopathy of prematurity. In a separate study from Tanzania, Vayu brand bubble CPAP (bCPAP) implementation was associated with immediate improvement in respiratory function [11]. While these and similar findings validate the hypothesis that bundling evidence-based clinical tools with skills mentoring and practice can drive rapid improvements in survival in high-burden settings, the implementation of advanced newborn care in Sierra Leone remains limited due to equipment shortages and gaps in provider training [12,13,14,15,16]. In light of the country’s position among the 15 countries with the highest NMRs worldwide, overcoming these barriers is an urgent priority.

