#### 2.4.1. Clinical Effectiveness Outcomes

The primary clinical outcomes focus on immediate survival and severe morbidity:Primary Neonatal: Reduction in the neonatal mortality rate within the first 24 h.Primary Maternal: Reduction in the incidence of postpartum hemorrhage (≥500 mL).Secondary Outcomes: Fresh stillbirth rate, institutional maternal case fatality rate, neonatal transfer rate for advanced care, and survival rate of sick newborns admitted to the SCBU.

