### 2.5. Outcome Measures

Outcome indicators, definitions, and data sources are summarized in Table 2. Primary outcomes are institutional maternal mortality, neonatal mortality within 24 h of birth, intrapartum stillbirth, and PPH incidence. Secondary outcomes include process indicators (e.g., uterotonic coverage for AMTSL, proportion of obstetric admissions receiving triage ultrasound) and intermediate clinical indicators (e.g., proportion of sick newborns initiated on bCPAP, SCBU survival).

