**Figure 2 mps-09-00096-f002:**
[figure not shown]
Implementation logic model.

**Table 1 mps-09-00096-t001:** Baseline characteristics and target training populations of participating healthcare facilities (2023).

Facility Name	Location (City)	Number of Annual Births	Maternal Deaths (2023)	Neonatal Deaths (2023)	Number of Annual C/S	Healthcare Workers Trained in Past 2 Years	Total Healthcare Workers to Be Trained
Bo Government Hospital	Bo	3226	34	191	1053	28	23
Jenner Wright Clinic	Freetown	412	17	6	14	13	-
King Harman Road Government Hospital	Freetown	712	8	15	331	9	87
Kissy CHC	Freetown	440	17	4	3	19	-
Princess Christian Maternity Hospital	Freetown	7099	63	464	3016	12	125
Rokupa Government Hospital	Freetown	1495	1	54	599	5	65
Ross Road CHC	Freetown	626	3	1	3	29	-
St. Anthony’s CHC	Freetown	511	19	2	5	27	-
Waterloo CHC	Waterloo	1015	17	11	20	8	23

**Table 2 mps-09-00096-t002:** Education and training.

Category	Indicator	Definition
Training uptake	Number of healthcare workers trained	Total number of midwives, nurses, physicians, and other staff completing WHO ENCC and PPH training modules
	Training completion against targets	Number completing training/facility training target
Skills retention	Frequency of LDHF practice sessions	Number of documented low-dose, high-frequency practice sessions per facility
	OSCE performance scores	Percentage of participants achieving competency on Objective Structured Clinical Examinations (OSCEs)
	Skills retention at 12 months	Percentage of trained staff maintaining competency at 12-month reassessment
Mentorship and supervision	Mentorship visits completed	Number of supportive supervision and mentorship visits conducted per facility
	Practice corner utilization	Frequency of use of facility-based LDHF practice stations

**Table 3 mps-09-00096-t003:** Maternal and newborn measures with definitions.

Category	Indicator	Definition
Maternal indicators	PPH incidence (500 cc)	[# of PPH incidence (500 cc)]/[total births]
	Uterotonics used for PPH prevention	[# of uterotonics used for PPH prevention]/[total births]
	Direct obstetric case fatalities	[# maternal deaths]/[# of total births]
	Admission triage scans	[# of ultrasound scans]/[# of maternal admissions]
	Abnormal scan findings	[# of abnormal scans]/[# of scans]
Neonatal indicators	Fresh stillbirths	[# of fresh stillbirths]/[total births]
	Neonatal case fatality rate < 24 h	[# of neonatal deaths < 24 h]/[total births]

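### Table 3 divides the primary 24-hour neonatal outcome by total births, not live births: the reported level is a few per cent too low, while the before-after ratio is hardly affected

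*Protocol article*

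**What the plan says.** Section 2.4.1 gives the primary neonatal outcome as "Reduction in the neonatal mortality rate within the first 24 h". Section 2.5 lists it again among four primary outcomes: "Primary outcomes are institutional maternal mortality, neonatal mortality within 24 h of birth, intrapartum stillbirth, and PPH incidence".

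Section 2.5 points to Table 2 for definitions, but the clinical definitions stand in Table 3. There the measure is labelled "Neonatal case fatality rate < 24 h", and its formula is "of neonatal deaths < 24 h]/[total births". The <48 h row has the same form. The fresh-stillbirth row is "of fresh stillbirths]/[total births", so one denominator serves both outcomes. The article does not define total births.

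Where Section 1.1 gives a neonatal mortality rate, it is per live births: "the neonatal mortality rate (NMR) remains high at 31 per 1000 live births".

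Section 1.4 sets targets of a 50% reduction in deaths within 24 h and a 10% reduction in fresh stillbirths. Section 2.7 compares the three months before implementation with the last three months of the project.

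**The concern.** Only a liveborn baby can die in the neonatal period, so a neonatal mortality rate takes live births as its denominator, as the article's own background does. The Table 3 formula very probably adds stillborn babies, who are not at risk. The label does not fit either: a case fatality rate is taken among cases, and total births are not cases.

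Two things follow. The figure reported under the name of a mortality rate is too low. It also depends on the proportion of stillbirths, which the bundle aims to reduce, so a change in stillbirth alone would move the primary neonatal outcome. What is at stake is mainly the level and meaning of the reported rate, and only to a small extent the before-after comparison.

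**Working it through.** **Inputs from the article.** Denominator: total births (Table 3). Target risk ratio for deaths within 24 h: 0.50. Target reduction in fresh stillbirths: 10% (both Section 1.4). Annual births in Table 1: 3226 + 412 + 712 + 440 + 7099 + 1495 + 626 + 511 + 1015 = 15,536, or 15,536/4 = 3,884 per three months.

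**Inputs assumed.** The article gives neither the stillbirth share of total births, *s*, nor a baseline 24 h mortality. I take *s* = 3-8% as the main range and 2-10% as a wider one. The article states no figure for this outcome that could be reproduced.

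**Does total births include stillbirths?** The term is undefined. For the fresh-stillbirth row to be a proportion, its denominator must contain stillbirths. That makes inclusion a strong inference, not a stated fact.

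**Level.** Table 3 rate = (rate per live birth) × (1 − *s*). To recover the rate per live birth, multiply by 1/(1 − *s*):

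| *s* | 1/(1 − *s*) | Table 3 rate needs raising by |
|---|---|---|
| 3% | 1.031 | 3.1% |
| 5% | 1.053 | 5.3% |
| 8% | 1.087 | 8.7% |

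Over the wider range the correction runs from 2.0% to 11.1%.

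**Before-after ratio.** With shares *s*0 at baseline and *s*1 at the end, ratio per total births = ratio per live births × (1 − *s*1)/(1 − *s*0). I apply the 10% target to the whole share, *s*1 = 0.9 × *s*0. This is generous, because the target covers fresh stillbirths only.

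| *s*0 | (1 − *s*1)/(1 − *s*0) | A true 0.500 reads as |
|---|---|---|
| 2% | 0.982/0.980 = 1.002 | 0.501 |
| 3% | 0.973/0.970 = 1.003 | 0.502 |
| 5% | 0.955/0.950 = 1.005 | 0.503 |
| 8% | 0.928/0.920 = 1.009 | 0.504 |
| 10% | 0.910/0.900 = 1.011 | 0.506 |

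When stillbirths fall the factor exceeds 1, so a real reduction looks slightly smaller. Larger errors need larger falls. From 8% to 6% the factor is 0.94/0.92 = 1.022, and from 8% to 5% it is 0.95/0.92 = 1.033. These are falls of 25% and 37.5%, well beyond the target.

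**Power.** In an illustrative two-proportion calculation (3,884 births per period, 24 h mortality assumed at 1-3%, halved), the denominator changes power by at most about 1.5 points: 68.1% on live births against 66.7% on total births, at 1% mortality and *s* = 10%.

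**Rescued babies who die early (invented counts).** Take 1000 births, 50 stillbirths and 20 deaths within 24 h. Suppose five stillbirths become live births and two of those babies die within 24 h.

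- Per total births: (22/1000)/(20/1000) = 1.100.
- Per live births: (22/955)/(20/950) = 1.094.
- Stillbirth plus <24 h death per total births, counting all 50 as fresh: (45 + 22)/(50 + 20) = 67/70 = 0.957.

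Three more babies survive, yet the <24 h rate rises by 9-10% under either denominator. Only the combined measure moves the right way.

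**The case against.** The strongest reply is that the planned conclusion would not change. Both periods use the same formula, the target is relative, and at the plan's own stillbirth target the ratio shifts in the third decimal place, in the conservative direction. That stands. A reader might infer that the choice of denominator manufactures or exaggerates a benefit; the arithmetic shows the reverse if stillbirths fall.

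A reader might also infer that the Table 3 figure fails because it cannot be set against the national rate of "31 per 1000 live births". The article does not support this. Section 1.1 defines that rate over 28 days, so a facility rate within 24 h is not comparable with it under either denominator, and no such comparison is planned. Section 1.1 shows only what denominator the article itself attaches to the term.

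A third tempting reading is that a live-birth denominator would deal with resuscitated babies who die early. It would not, as 1.100 against 1.094 shows. Total births even has a merit here: it is unchanged when a death is reclassified between stillbirth and early neonatal death, and the two Table 3 rows can be added directly. That is a good reason to report the combined outcome, but not to call the <24 h row a mortality rate.

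Finally, inclusion of stillbirths is inferred and the stillbirth share is assumed. Both are fair limits. If total births in fact meant live births, the neonatal rows would need only correct wording.

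**Conclusion.** The concern holds as a mismatch of definition with a modest numerical effect. The primary neonatal outcome is named a mortality rate but defined as something else, and its level comes out too low, needing to be raised by about 3-9% at stillbirth shares of 3-8%. The before-after ratio is off by 0.3-0.9% over that range at the 10% stillbirth target (1.1% at a share of 10%), towards no effect if stillbirths fall.

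This rests on total births including stillbirths, strongly implied by the fresh-stillbirth row, and on an assumed stillbirth share. It does not make the before-after comparison invalid. The change is worth making because this is a primary outcome, its formula is fixed in the article, and the correction is specific and cheap.

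**What to change.** 1. In Table 3, change the denominator of the <24 h row to live births and rename it neonatal mortality rate <24 h, matching Sections 2.4.1 and 2.5. Do the same in the <48 h row for consistency; that row is not among the primary or secondary outcomes named in Sections 2.4.1 and 2.5.
2. Define total births and live births in a table note, and apply the definitions identically to the baseline and final periods.
3. Report fresh stillbirth plus death within 24 h, per total births, alongside the primary outcome, to cover movement between stillbirth and early death.

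The cost is small but not nil. Table 3 lists no live-birth count, and total births minus fresh stillbirths would not give one because other stillbirths are not listed. The count should be available from the maternity and newborn registers that Section 2.6 already plans to extract, though the article does not say so; this should be confirmed for the retrospective baseline. The combined measure needs no new data, since both numerators and the denominator are already in Table 3.

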### 1.3. Implementation Logic Model

The implementation logic follows a pathway in which resource inputs lead to enhanced clinical capacity and improved outcomes.

Inputs: Newborn: Vayu bCPAP, oxygen blenders, resuscitation equipment, monitors, oxygen concentrators, and consumables. Maternal: hemorrhage quantification and treatment tools, Butterfly ultrasound, Hemocue, heart tone Dopplers, and consumables.Activities: Training in ENCC Parts 1 and 2, Vayu bCPAP training, WHO PPH Course, and basic ultrasound diagnosis training; establishment of facility-based “Champions” and LDHF practice corners. Monthly mentoring, supportive supervision, and scale-up assistance.Outputs: We anticipate timely resuscitation (within one minute) and improved treatment of respiratory distress, in addition to improved maternal risk stratification and management of PPH.Outcomes: We anticipate a reduction in perinatal mortality, improved SCBU neonatal survival, and decreases in PPH incidence, institutional maternal mortality, and morbidity.Impact: We anticipate a sustained reduction in maternal and neonatal mortality and morbidity, contributing to SDG targets.

This implementation logic model is based on the following assumptions:There will be sustained political support for this project.Supply chain systems will ensure maternal and newborn commodity security across supported facilities.Staff will remain committed to project implementation.

The main components of the project plan, as outlined above, are shown in Figure 2.

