### 1.4. Objectives

The primary objective of implementing a targeted service delivery bundle is to enhance maternal and newborn outcomes in a cohort of nine hospitals over a three-year period. These service delivery improvements aim to achieve the following:Reduce neonatal mortality: Achieve a 50% reduction in neonatal deaths within the first 24 h and a 10% reduction in intrapartum or “fresh” stillbirths compared to a baseline assessment.Reduce neonatal morbidity: Achieve a 25% reduction in neonatal transfers to advanced care.Improve neonatal clinical practice: Ensure that 80% of SCBU admissions with respiratory distress receive appropriate oxygen therapy.Reduce maternal morbidity: Achieve a 40% reduction in the incidence of postpartum hemorrhage and a 50% reduction in institutional maternal mortality.Improve obstetric clinical practice: Ensure that 90% of deliveries utilize active management of the third stage of labor with uterotonics to prevent hemorrhage.Strengthening diagnostic capacity: Deploy handheld ultrasound and point-of-care hemoglobin testing to improve obstetric risk stratification.Maintain competency: Implement a “train-the-trainer” model, mentoring, low-dose high-frequency practice, and supportive supervision to maintain high performance on knowledge and skills checks at 12-month intervals.

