	Neonatal case fatality rate < 48 h	[# of neonatal deaths < 48 h]/[total births]
	Neonatal transfers from maternity	[# of neonatal transfers from maternity]/[total births]
	Sick newborns on bCPAP	[# on bCPAP]/[# of SCBU admissions]
	Survival of sick newborns	[# survive SCBU admission]/[# of admissions]

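### Survival per SCBU admission is a secondary effectiveness outcome whose denominator the bundle can itself change, so a crude before-after comparison cannot separate better treatment from a changed case mix

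*Protocol article*

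**What the plan says.** Section 2.4.1 places the "survival rate of sick newborns admitted to the SCBU" among the secondary outcomes under clinical effectiveness. Section 2.5 also makes it secondary, but groups it with the "intermediate clinical indicators (e.g., proportion of sick newborns initiated on bCPAP, SCBU survival". The logic model in Section 1.3 counts "improved SCBU neonatal survival" as an anticipated outcome, so a rise is to be read as benefit.

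Table 3 gives the definition, "survive SCBU admission]/[# of admissions": survivors of an SCBU admission over SCBU admissions. Section 2.7 compares the three months before implementation with the last three months of the project by analysis of variance, t-tests and chi-square.

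Table 3 divides fresh stillbirths, neonatal deaths before 24 h, neonatal deaths before 48 h and transfers from maternity by total births. No death indicator with that denominator runs beyond 48 h. The limitations in Section 3.5 name outside influences and register quality, but not a change in SCBU case mix caused by the bundle.

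**The concern.** Admission to the SCBU is decided after the bundle has begun to act, and the protocol's own aims bear on who is admitted:

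- Section 1.4 sets the targets "Achieve a 50% reduction in neonatal deaths within the first 24 h" and 10% fewer fresh stillbirths. Some babies saved in this way will be very sick and will reach the SCBU.
- The same section sets the target "Achieve a 25% reduction in neonatal transfers to advanced care". If those transfers feed the SCBU, admissions shrink.
- Section 2.3 brings in pulse oximeters, bubble CPAP, blenders and newborn-care training, and Section 1.3 says "We anticipate timely resuscitation (within one minute) and improved treatment of respiratory distress". Better recognition and new capacity can widen admission to milder babies.

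These forces pull in different directions, so the sign of any bias cannot be known in advance. The babies admitted in the baseline and final quarters may differ in severity, and a crude proportion compares them as if they were alike. At stake is how this secondary outcome is read: a rise could be reported as a treatment benefit with no death averted, or a fall as harm while more babies live.

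**Working it through.** The document states no baseline, target or sample size for SCBU survival, so there is no figure of its own to reproduce. The check is arithmetic on S = 1 − D/A, where D is SCBU deaths and A is SCBU admissions, both per 1000 births. All values of A, of case fatality and of deaths before admission are assumptions.

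**Simple illustration (A = 100, D = 25, S = 75%)**
- Fifty further mild babies are admitted and all survive: (75 + 50)/150 = 83.3%. Deaths stay at 25.
- Ten babies who would have died at birth are resuscitated and admitted, and five survive: (75 + 5)/110 = 72.7%. Five more babies live.

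**Wider ranges (A from 100 to 300; case fatality 10%, 20% or 30%)**
- (a) 25% more admissions, all mild, same deaths: S = 1 − D/(1.25A). Survival goes from 90.0% to 92.0%, from 80.0% to 84.0%, and from 70.0% to 76.0%.
- (b) 25% fewer admissions, all removed babies being ones who would have survived, same deaths: S = 1 − D/(0.75A). Survival goes from 90.0% to 86.7%, from 80.0% to 73.3%, and from 70.0% to 60.0%.
- (c) Rescue to admission: 10 to 20 pre-admission deaths per 1000 births are halved, giving x = 5 to 10 extra admissions with SCBU mortality q of 40% to 60%. Then S = 1 − (D + xq)/(A + x), and total deaths fall by x(1 − q). At 20% case fatality, survival falls from 80.0% to between 76.4% and 79.7%, while total deaths fall by 5 × 0.4 = 2 to 10 × 0.6 = 6 per 1000 births. Worst case: 1 − (20 + 6)/110 = 76.4%, while total deaths go from 20 + 20 = 40 to 26 + 10 = 36.

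**Could a chi-square test call a pure artefact significant?** Annual births in Table 1 sum to 15,536, or 3,884 per three months. At an assumed 100 to 200 admissions per 1000 births, the baseline quarter has about 388 to 777 admissions. With 80% baseline survival and a two-sided 5% level, artefact (b) would be declared significant with probability 53% to 82%, and artefact (a) with probability 34% to 58%.

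**Which per-birth measure has the right sign?** Take the ten-baby rescue again.
- SCBU deaths alone per 1000 births go from 25 to 30. This looks 20% worse although five more babies live.
- If the ten would have been live-born delivery-room deaths, all pre-discharge neonatal deaths go from 25 + 10 = 35 to 25 + 5 = 30.
- If the ten would have been fresh stillbirths, neonatal deaths go from 25 to 30 while fresh stillbirths fall by 10. The two together fall by 5.

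So the measure must count all neonatal deaths before discharge and be read alongside fresh stillbirths.

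**The case against.** The strongest reply is that little depends on this ratio. It is secondary, Section 2.5 calls it intermediate, and Section 1.4 sets no target for it; the target there for respiratory support concerns the use of appropriate oxygen therapy. The primary neonatal death outcome is per birth. Much of the rescue benefit would show in fresh stillbirths and deaths before 24 h and 48 h, none of which is conditioned on admission. This stands, and it limits the weight of the point.

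A reader might infer that SCBU survival will carry the conclusion on bubble CPAP, or that it is the only clinical outcome covering babies so treated. The documents support neither. No text assigns it that role, and the 24 h and 48 h indicators include early SCBU deaths. What remains is narrower: it is the only listed outcome that sees SCBU deaths after 48 h.

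A reader might also take the scenarios as estimates of bias. They show possibility only. The large rise needs 50% more admissions, all mild, which sits uneasily with a target of fewer transfers. Scenario (b) in turn assumes that the transfers in Section 1.4 are SCBU admissions, which the document does not say.

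Finally, case-mix tabulation may be specified in a fuller plan that is not shown. That is fair, and the point does not rest on its absence. It rests on the stated definition together with the stated effectiveness role.

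**Conclusion.** The concern holds for one secondary outcome. As defined, SCBU survival per admission cannot distinguish better treatment from a changed case mix, and it can move either way without a matching change in deaths. Under the assumptions shown, with 80% baseline survival, the artefact ranges from a rise of 4 points to a fall of 6.7 points; its true size and direction are unknown. Confidence is high in the mechanism, not in any magnitude. The primary neonatal death outcome, being per birth, does not have this defect. The change is worth making because it is cheap and prevents a misleading effectiveness claim, not because the overall conclusion would otherwise fail.

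**What to change.** In Table 3, add as the effectiveness measure all pre-discharge neonatal deaths among babies born in the nine facilities, wherever in the facility they die and including the SCBU, per total births. Read it together with fresh stillbirths per total births. Do not use SCBU deaths alone per birth, which rise when babies are rescued to admission.

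Keep survival per SCBU admission, labelled descriptive in Sections 2.4.1 and 2.5. Report it beside SCBU admissions per total births in each period, and stratify it by birth-weight band and inborn/outborn status where the registers record them. Add case-mix change to the limitations in Section 3.5.

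The cost is protocol wording and mostly re-tabulation, since Section 2.6 already plans granular extraction from the maternity and newborn registers. The document does not say that birth weight or place of birth is recorded there, so stratification depends on that. There is some added work: inborn and outborn admissions must be separated, and deaths linked across maternity and SCBU registers before the data are aggregated by facility. No clinical care changes.
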